***Data Storage and Confidentiality***

The CTCC will initially provide each site with a block of 100 subject identification numbers. The site will sequentially assign these numbers as subjects are prescreened for participation in the study. The CTCC will not have any access to subject names. At the conclusion of the baseline visit, the site will log on to the new clinical data management system using a unique User ID/Password combination that will limit access to enter and view data specifically for subjects at their site. While in this system the individual will use the electronic data capture tool to indicate that the subject has enrolled into the study. All source documents and case report forms will be labeled with the subject identification number. The subject will also be identified with a CTCC Unique Identification number. The CTCC Unique ID system was designed and implemented in response to the desired ability to track individual subjects across multiple studies without storing any personally identifiable information.

The system uses an algorithm, which takes as input nine data elements (last name, first name, gender, day of birth, month of birth, year of birth, city of birth, country of birth, and mother’s maiden name) and produces as output a "fingerprint" of the input. These 9 data elements were chosen as the least likely to change for an individual thus minimizing the likelihood of multiple numbers for an individual. CTCC uses the NIST/NSA designed hash function known as SHA512 because there is no known way to reverse or ‘decrypt’ the 9 data elements. It is completely a one-way function. The system then stores only the fingerprint and clears the individual’s responses from memory. The user is then assigned a number, which is associated to their fingerprint. Users never have access to the fingerprint resulting in a further level of protection. All system components are protected behind a Cisco firewall device and the individual’s responses are protected by a 128-bit secure socket layer (SSL) encryption to their point of entry.

Once the subject has signed the consent form for COHORT, the subject is directed to an accessible website (<https://www.ctcc.rochester.edu/uniqueid>) where they will enter the nine data elements as delineated above, which should not change over time. The fingerprint will be coded to a 9-digit unique identification number. This number will be provided to the subject and the coordinator will record this number on the Demographics case report form for COHORT. If at any point the subject forgets his or her unique CTCC identification number, he or she can go back to the website and enter the 9 data elements again. These 9 data elements must be identical to those entered before to obtain the same unique ID. The computer program will create the same fingerprint and return the same unique identification number.

Coriell will assign a unique repository identification number to each sample, which is different from the subject identification number and the CTCC unique identifier assigned by the CTCC**.** Blood cellDNA and DNA from the lymphoblastoid cell line sent to Massachusetts General Hospital DNA Genotyping Laboratory for genotyping will be coded and only identified by the Coriell identification number. The CTCC and Coriell will be able to link the subject identification number and the Coriell identification number, but neither Indiana nor the MGH DNA Genotyping lab will be able to link the subject number with the Coriell identification number.

All plots of family history data generated at Indiana will be created without any identifying family information (such as names). The family history data are stored on a computer running Microsoft Windows 2000 Server. This operating environment has been evaluated by the International Organization for Standardization (ISO) and meets the Common Criteria (CC) EAL 4 security rating. In addition, Windows 2000 Server provides security features over and above the EAL 4 level with the Microsoft Security Response Center. Databases are backed up daily to tape.

***Certificate of Confidentiality***

A Certificate of Confidentiality has been obtained from the Department of Health and Human Services. This certificate will be used to enhance the confidentiality for subjects in COHORT given many of the research subjects have HD or are “at-risk” for HD. The extra layer of protection is a necessity considering the potential disclosure of gene or clinical status could cause negative employment, difficulty obtaining insurance, and social or familial consequences. In addition, since subjects themselves will also remain blinded to their gene testing results, involuntary disclosure could have a negative impact on an individual’s psychological well-being and mental health.

# RISK/BENEFIT ASSESSMENT

1. **Potential Risks**

***Blood draw*** – The collection of blood specimens may cause pain and/or bruising at the site where blood is drawn. Fainting or feeling lightheaded may occur during or shortly after having blood drawn. If a subject experiences this, the subject will be instructed to lie down immediately to avoid possible injuries. Localized clot formation and infections may occur, but this is very rare.

***Unified Huntington’s Disease Rating Scale/Mini-Mental State Examination/Family History Questionnaire*** – The subject may experience anxiety or psychological discomfort while completing the UHDRS 99, MMSE, and family history questionnaire.

***Breach of Confidentiality*** – There is always the possibility of a breach of confidentiality with information that is entered into a computer database. Someone could breach the security of the computer system(s) and access information, thereby resulting in a loss of confidentiality. During the course of this study, it is possible that the investigators may develop concerns about the subject causing harm to themselves or others. In these situations, confidentiality may be breached in order to protect the subject or others.

1. **Protection Against Risks**

Blood draw/UHDRS 99/MMSE

Only experienced staff will draw the blood for this study. The UHDRS 99 and MMSE data will be labeled with only the subject identification number.

***Event Monitoring Committee***

The Event Monitoring Committee (EMC) will periodically review coded data from the COHORT study for potential safety concerns. The committee will then advise the Steering Committee about findings relevant to the conduct of the trial, and assist in training or other efforts related to human subjects issues. In the mode of a data monitoring committee, the EMC will:

1. Analyze and categorize the occurrence of pre-specified medical and mental health events;
2. Periodically advise the principal investigator and steering committee about the occurrence and significance of pre-specified medial and mental health events;
3. Develop and recommend policies related to these events;
4. Participate in or facilitate the public dissemination of the findings, via peer-reviewed publications, in concert with the Principal Investigators and Steering Committee.

The EMC may recommend that certain issues or concerns be reviewed by: 1) the Principal Investigator or Steering Committee; 2) the medical monitor; 3) the standing HSG Bioethics Advisory Committee (BAC); or 4) the standing HSG Scientific Advisory Committee (SAC).

CTCC Protections Against Breach of Confidentiality

The CTCC has several provisions in place to maintain integrity, confidentiality, and security of subject information. The CTCC computer systems and networks are managed by full-time system administrators. All (internal relational databases and programming server) network traffic is sent across a cisco switched network behind a Cisco PIX 515 Firewall. All PC’s run virus protection software full-time and are updated with the latest virus definitions and scanned on a regular schedule; the Windows servers are protected as well and we have additional security in place to scan all e-mail for viruses before a user has access to them. All servers have been customized to run the bare minimum of network services in order to minimize potential “back door” attacks, and both servers are updated on a regular basis with the latest vendor recommended software patches and updates. In addition, other security software runs continuously minimizing the potential for other threats (e.g., password “crackers” to detect easily guessable passwords). All accounts are password protected and passwords must be changed on a regular basis. All study data is stored in a relational database management system residing on one of several UNIX servers. Each study database has multiple security levels including: network access to the server, access to the database, group level access, and access to individual tables, views, and stored procedures within a database. In general, users are set up with the minimal required level of access to database objects, e.g. if a user requires read-only access to a table then he/she is set up that way. For web-based applications, SSL security is employed to protect all network traffic.

All servers reside in one of several racking systems inside a locked computer room that is physically accessible only by the departmental system administrators. The computer room is temperature controlled and has water sensors in the ceiling to alert system administrators in case of a leak from above. It is also equipped with smoke/fire detection sensors and motion sensors. To ensure high system availability the Sun server is equipped with dual power supplies. Each night the system does an “epoch” backup to SDLT tape and each private subnet.

All CRF data and other critical study data are fully audit trail enabled so that all changes to the data can be monitored and/or recovered. Permissions are carefully maintained to allow only the required level of access to study data. Files and directories are carefully set with only the required level of access.

***Indiana University Protections Against Breach of Confidentiality***

Extensive security measures have been taken to ensure the privacy and confidentiality of all data that will be sent to Indiana University. Files containing family information are housed in a secure location within the Department of Medical and Molecular Genetics at the University of Indiana. Computer files are stored on a SUN microcomputer, which is housed in a secure room within the Department of Medical and Molecular Genetics. Security of data is protected by the following authentication process: 1) the user must log in by supplying a user-name and password. Password changes are enforced on a regular basis and unsuccessful login attempts are logged and the administrator is notified.  Accounts are locked-out after several consecutive unsuccessful login attempts; 2) Access to the data is limited not only to specific users but also to the location from which they are logging-in.  A login will fail if it is not from a computer at a trusted Internet address; and 3) once the domain login is authenticated, the user must supply another database-specific password to access the data. Databases are backed-up daily to local disk and archived weekly to tape.  Use of a microcomputer for data storage has many advantages over the use of mainframe computers, the greatest of which is heightened security. In addition, the SUN operating system, SOLARIS, is a Unix system that allows for ease of data entry and query processing. Every precaution has been taken to assure that computer confidentiality is maintained.

Coriell Institute for Medical Research (Coriell Cell Repositories) Protections Against Breach of Confidentiality

The Coriell Cell Repositories has several provisions in place to maintain integrity, confidentiality, and security of its data and information systems. Coriell does not store subject’s confidential information, has security policies in place to assure that all data are protected from unauthorized access, and maintains audit trails, backup procedures and error checking to assure accuracy and protection of its data.

Protection of Subject Confidentiality Provisions

As part of the operation of its many repositories, Coriell has been proactive in maintaining the confidentiality of its donor subjects. When a sample is submitted to Coriell, it is assigned a unique repository identifier, generally a seven digit alphanumeric: the first two digits are letters indicating the repository into which it will be accessioned, and the next five digits are numbers generally beginning with 00001 assigned sequentially to each sample as it arrives at Coriell. Through all operations at Coriell, the materials are tracked using this unique identifier. There is no identification of the submitting investigator for materials that are displayed in an electronic catalog to prevent individuals from establishing the identity of the donor subject.

Coriell has its own Institutional Review Board that consists of thirteen members, six of whom work at the Institute and seven from outside the Institute. Coriell's IRB will not be utilized for this study, as the Coordination Center IRB and all of the site IRBs will review this protocol. In addition, each of the faculty members at Coriell has received Human Subjects Assurance Training and is certified through the Office for Human Research Protections.

Although Coriell is not a HIPAA covered entity, it must work directly with HIPAA covered entities both in its acquisition phase and in its distribution phase. The information in the 18 identifiers that is restricted under HIPAA is not collected at Coriell and submitters are requested not to submit such information. The lack of this information does not reduce the value of the Repositories in any way, and Coriell will continue to monitor changes in the interpretations of the HIPAA regulations.

*Network Security Provisions*

The computer systems, servers and network are maintained with full-time system administrators, and the Coriell network administrator is responsible for maintaining a secure network environment. The administrator monitors security logs on a regular basis to ensure network integrity. The administrator also manages the account credentials for all users on the network. The superuser passwords on all servers are changed every three months for additional security. The Coriell firewall is a Cisco PIX Firewall device and is configured to route traffic to a DMZ zone and an internal zone. The DMZ zone includes the servers that need to be accessed publicly, such as the web and email servers. The internal zone includes the database servers and all desktop computers. This network configuration establishes a secure environment that minimizes the risk of unauthorized access from external networks.

All desktop computers run virus protection software full-time and are updated with the latest virus detection strings regularly.

*Data Security Provisions*

The hardware platform Coriell currently uses for its collection/specimen data capture, storage, and analysis is a SUN SPARC Enterprise 450; this server is dedicated exclusively to these tasks. The SUN server resides in a racking system inside a locked server room that is physically accessible only by the Information Systems staff. The server room is equipped with smoke/fire detection sensors. To ensure high system availability the SUN server is equipped with dual power supplies, hot-swappable RAID 5 disk drives, and an APC uninterruptible power supply. The Relational Database Management Software suite is Sybase 11.9.2 (Adaptive Enterprise Server). Running concurrently with the Sybase database is the Sybase Backup Server that performs full daily backups of the Coriell databases.

Sybase contains an elaborate and comprehensive security system based on user rights and permissions. This security system is fully utilized to allow only the necessary personnel to insert or update data in the production database. For any item of data that is entered in the data repository, an audit trail record will be generated by the system.

Coriell protects against the accidental loss of valuable data by establishing documented backup and recovery procedures on a daily basis.

***Massachusetts General Hospital (MGH) DNA Genotyping Laboratory Protection Against Breach of Confidentiality***

All samples sent to MGH DNA Genotyping Laboratory for CAG genotyping and genotyping of authenticated polymorphisms in other genes previously shown to modify timing or expression of disease features will be coded. For the purposes of genotyping the lab at MGH will receive no subject data or identifying information. They will receive the blood DNA samples and the DNA from the lymphoblastoid cell line with only the Coriell Identification Number.

1. **Potential Benefit**

##### Subjects will receive no medial benefit from participation in this study. The only potential benefit is a better understanding of HD and the possibility that the information obtained in this study lead to potential treatments and to plan future research studies of experimental drugs aimed at slowing or postponing the onset of HD.

1. **Alternatives to Participation**

The only alternative to participation in this study is not to participate.

1. **Withdrawal from Participation**

Subjects may be withdrawn from the study for the following reasons:

- - - - A change in medical condition, so that remaining in the study might risk an individuals health or the research.
      - Failure to complete the required study procedures, regardless of reason.
      - The site investigator feels that it is in the best interest of the subject.

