COHORT is the centerpiece of the Huntington Project (<http://www.huntingtonproject.org/>), a worldwide collaborative undertaking to develop treatments that make a difference for HD. The Huntington Project and COHORT are sponsored by HP Therapeutics Foundation, Inc., a not-for-profit corporation that supports a variety of research projects seeking to find treatments for Huntington's disease. COHORT was planned and is overseen by the Huntington Study Group (HSG), (<http://www.huntington-study-group.org/>), a not-for-profit consortium of researchers established in 1993 to improve treatments for HD. The HSG now comprises more than 70 sites worldwide and has carried out 10 multi-center observational and interventional studies involving more than 10,000 individuals affected by HD. COHORT builds on the accrued HSG databases from these studies and its established network of investigators and research subjects.

HD is a uniformly progressive neurodegenerative disorder characterized clinically by movement disorder (typically chorea), behavioral disturbances, and cognitive impairment. The mean age of HD onset is approximately 39 years, after which illness progresses steadily over a period of 15-25 years. Approximately 30,000 people in the United States have clinical manifestations of HD, and an additional 150,000 unaffected individuals (about 60,000 HD gene carriers and 90,000 non-HD gene carriers) are immediately at risk to develop HD. In the United States, only about 5-10% of individuals at immediate risk for HD have chosen to undergo pre-symptomatic DNA testing to learn if they carry the HD gene.

The steady worsening of the motor, cognitive, and behavioral features of HD results in progressive functional decline. Clinical rating scales that chart the progression of illness have been widely used to establish the rate of functional decline in a variety of HD populations.[[18]](#endnote-19),[[19]](#endnote-20),[[20]](#endnote-21),[[21]](#endnote-22),[[22]](#endnote-23),[[23]](#endnote-24) The extent of functional disability correlates well with the extent of basal ganglia degeneration detected by neuroimaging and postmortem examination.Error: Reference source not found,[[24]](#endnote-25),[[25]](#endnote-26),[[26]](#endnote-27),[[27]](#endnote-28)

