Protecting confidentiality has been an overriding principle in the development and design of COHORT. The broad nature of the inclusion criteria creates a unique situation in which varying levels of concern regarding confidentiality will be apparent. COHORT was designed to provide a flexible situation in which subjects are given the ability to decide the procedures in which they will participate. The collection of clinical information and blood for CAG/genetic polymorphism analyses are the only required procedures in COHORT. Optional procedures include the collection of family history information and the storage of biological specimens in the repository.

While there is scientific merit for including both affected and unaffected individuals under the age of 18, only children with clinically diagnosed features of HD in the setting of a confirmatory family history or clinically diagnosed features of HD with a positive gene test will be eligible to participate in COHORT. Those children who are eligible to enroll will only participate in the phenotypic evaluation, which includes the neurological and physical examination, medical history, and the UHDRS 99. Children will only participate in the phenotypic evaluation until we are able to further evaluate the process by which these children will be able to ethically and safely participate in the other aspects of this study. Unaffected children will not be enrolled at this time because of concern over the potential psychological consequences of including this population in COHORT. In the future, this study may be amended to include these additional populations and procedures.

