###### Confidentiality is a major concern for most individuals who have HD or are at risk of having HD. Therefore, subjects will be given the option of allowing the study staff to contact them between study visits to collect additional information or to provide updates regarding the study. If a subject agrees, he/she will receive information about the study as it progresses and may be contacted between visits for additional clarifications. Confidentiality is of utmost importance, but to maintain the validity of the study, retention of subjects longitudinally is crucial. Although subjects will be given the option of receiving information as stated above, they will not be given the option for contact regarding study appointments. The study staff will work with each subject to set up the best method for contact between study visits for appointment confirmation and to reschedule any missed appointments.

- - - 1. **Family History Questionnaire (FHQ)**

Any subject 18 years of age and older with a family history of Huntington’s disease will be asked to complete the FHQ. This portion of the study is completely optional. The primary questionnaire will be completed only once during the study. The subject may complete the FHQ at the first visit or they may choose to complete the questionnaire at a subsequent yearly visit.

The subject will be given the option of completing the questionnaire during the study visit or of taking the questionnaire home and mailing it back to the site with a stamped, addressed envelope.. If the completed questionnaire is not received within one month of the study visit, the site will follow-up with the subject.

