The COHORT study was designed to assemble a large descriptive database that will provide the opportunity to study many different factors potentially associated with HD-related events. Some potential factors include history of smoking, current concomitant medication use, or an unknown gene possibly associated with a predisposition to HD. The primary outcome for those affected with HD is progression of disease, which is measured by a decrease in total functional capacity (captured on the UHDRS 99). The primary outcome for those at risk would be phenoconversion or clinical onset of disease.

The table below gives the numbers of events required to detect an increase in risk corresponding to a hazard ratio of the specified magnitude associated with a single risk factor with the specified prevalence. A two-sided alpha level of 5% is assumed. The numbers of events given are for 80% power; for 90% power multiply all entries by 1.34.

| **Risk Factor Prevalence** | **Hazard Ratio** | | | | | | | |
| --- | --- | --- | --- | --- | --- | --- | --- | --- |
| **5.0** | **4.0** | **3.0** | **2.5** | **2.0** | **1.8** | **1.6** | **1.5** |
| **1%** | 306 | 412 | 656 | 943 | --- | --- | --- | --- |
| **2%** | ***154*** | ***208*** | 331 | 476 | 833 | --- | --- | --- |
| **3%** | ***104*** | ***140*** | 223 | 321 | 561 | 780 | --- | --- |
| **4%** | ***79*** | ***106*** | ***169*** | 243 | 425 | 591 | 924 | --- |
| **5%** | ***64*** | ***86*** | ***137*** | ***197*** | 344 | 478 | 747 | --- |
| **6%** | ***54*** | ***72*** | ***115*** | ***166*** | 289 | 402 | 629 | 846 |
| **8%** | ***41*** | ***55*** | ***88*** | ***127*** | 222 | 308 | 482 | 648 |
| **10%** | ***34*** | ***45*** | ***72*** | ***104*** | ***181*** | 252 | 394 | 530 |
| **12%** | ***29*** | ***39*** | ***62*** | ***88*** | ***155*** | ***215*** | 336 | 452 |
| **14%** | ***25*** | ***34*** | ***54*** | ***78*** | ***136*** | ***188*** | 295 | 396 |
| **16%** | ***23*** | ***30*** | ***48*** | ***69*** | ***121*** | ***169*** | 264 | 355 |
| **18%** | ***21*** | ***28*** | ***44*** | ***63*** | ***111*** | ***154*** | 240 | 323 |
| **20%** | ***19*** | ***25*** | ***41*** | ***58*** | ***102*** | ***142*** | 222 | 298 |
| **25%** | ***16*** | ***22*** | ***35*** | ***50*** | ***87*** | ***121*** | ***189*** | 254 |
| **30%** | ***14*** | ***19*** | ***31*** | ***44*** | ***78*** | ***108*** | ***169*** | 227 |

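### The withdrawal clause permits, at each site's discretion, removal of affected subjects because HD stops them completing procedures, so dropout can depend on the progression outcome

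*Protocol*

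**What the plan says.** Section VII, Withdrawal from Participation, opens with "Subjects may be withdrawn from the study for the following reasons" and gives three grounds. One is "Failure to complete the required study procedures, regardless of reason". Another is "A change in medical condition, so that remaining in the study might risk an individuals health or the research". The third is the site investigator's view of the subject's best interest.

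Section III (Discussion of Study Design) defines what is required: "The collection of clinical information and blood for CAG/genetic polymorphism analyses are the only required procedures in COHORT". Section VIII a sets the outcome: "The primary outcome for those affected with HD is progression of disease, which is measured by a decrease in total functional capacity". That score comes from the UHDRS 99. Section II explains the mechanism: "The steady worsening of the motor, cognitive, and behavioral features of HD results in progressive functional decline".

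Other sections expect declining subjects to stay in the study:
- Section IV (Vulnerable Subjects/Subject Capacity) allows enrolment of people with HD who are already mentally incapacitated.
- Section V (Process of Consent) foresees loss of capacity during the study and recommends a research proxy to help decide on continued participation.
- Section VI b (UHDRS 99) lets an accompanying person support or add to the subject's answers.
- Section VI b (Contact Between Study Visits) says that "to maintain the validity of the study, retention of subjects longitudinally is crucial" and has staff reschedule missed appointments.

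For minors, section VI lets the investigator judge which parts of the UHDRS 99 the child can complete. No equivalent is stated for adults. Section VI a records deaths of subjects who are participating and describes nothing after withdrawal.

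**The concern.** COHORT gives no treatment, so there is no drug exposure to stop and little reason to end follow-up because a subject has become too ill to finish a battery. The UHDRS 99 takes about an hour. The motor, cognitive and behavioural worsening that lowers TFC is a foreseeable reason for failing to complete it, or for missing the visit. A clause that covers every reason includes that one.

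If a site uses the clause in this way, the chance of leaving depends on the functional level being measured, and the dropout is informative. The low scores and the vital status of those subjects are then never collected. An analysis plan can model what was observed, but it cannot recover what the conduct rule stopped sites from collecting. Follow-up is open-ended, so such losses would accumulate. The clause gives no criteria for its use, so approximately 41 sites may apply it differently.

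**Working it through.** **1. The plan's own figure.** Section VIII a needs 181 events for a hazard ratio of 2.0, risk factor prevalence 10%, two-sided 5% and 80% power. By Schoenfeld's formula, events = (1.960 + 0.842)² / [p(1−p)(ln HR)²] = 7.849 / (0.09 × 0.4805) = 181.5. The table reproduces and is not in question. The protocol gives no withdrawal rate, so every loss rate below is an assumption.

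**2. Events lost equally in exposed and unexposed.** Events left = 181 × (1−q). Underlying events needed = 181/(1−q), rounded up.

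| q lost | Events left | Power | Events needed |
|---|---|---|---|
| 10% | 162.9 | 75.6% | 202 |
| 20% | 144.8 | 70.6% | 227 |
| 30% | 126.7 | 64.8% | 259 |

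In this approximation the hazard ratio stays at 2.0.

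**3. Events lost unequally.** Approximate observed HR = 2 × (1−q₁)/(1−q₀). With q₁ = 20% in exposed and q₀ = 10% in unexposed, HR = 2 × 0.80/0.90 = 1.78. Events needed = 181 × (ln 2 / ln 1.78)² ≈ 263. The attenuation comes entirely from the assumed 2:1 ratio of losses, and no document supports that ratio. It is illustrative only.

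**4. Slope of functional decline.** A simulation used 3,000 subjects, a TFC-like score with baseline mean 9 (SD 2), mean decline 0.8 points/year (SD 0.4), error SD 0.7 and annual visits to year 5. The yearly withdrawal probability was m / (1 + exp(level − 5)), with m = 0.2, 0.5 or 0.8. It therefore depends on current level. Bias = 1 − estimated slope / true slope.

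| Failed visit's score | m | True slope | Completers (bias) | Mixed model, all visits (bias) |
|---|---|---|---|---|
| kept | 0.2 | −0.805 | −0.764 (5%) | −0.796 (1%) |
| kept | 0.5 | −0.794 | −0.701 (12%) | −0.771 (3%) |
| kept | 0.8 | −0.800 | −0.687 (14%) | −0.782 (2%) |
| not kept | 0.2 | −0.785 | −0.727 (7%) | −0.769 (2%) |
| not kept | 0.5 | −0.806 | −0.665 (17%) | −0.757 (6%) |
| not kept | 0.8 | −0.799 | −0.603 (25%) | −0.705 (12%) |

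Subjects lost had declined 0.23-0.34 points/year faster than those kept. The crude share with a recorded 3-point fall dropped from about 0.70-0.72 to 0.51-0.65 (score kept) or 0.38-0.59 (not kept). That crude share makes no allowance for censoring.

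**5. A second set of assumptions.** With mean decline 0.65 (SD 0.4) and loss once the score falls to 2-4, a mixed model on all visits was off by about 0-6% at baseline mean 9 and 4-15% at baseline mean 7. These ranges describe the scenarios tried. They are not bounds.

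**The case against.** The strongest reply is that the clause only permits withdrawal. It sets no trigger, and nothing says sites will use it on declining subjects. It has an ordinary administrative use: a subject who never gives the genotyping sample or never attends falls under it for reasons unrelated to decline. The proxy, companion and rescheduling provisions all point towards keeping people in. Failing the cognitive tests or the MMSE need not lose the TFC, which is largely a matter of questions that a companion can help answer. Calling retention crucial does not strictly contradict a discretionary ground.

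Most of this stands, and it limits the point. A reader might infer that the rule removes the fastest progressors and does bias the outcome. The documents do not support that. They show a permission, and exposure depends on low function, not on speed of decline as such. A subject who starts low and declines slowly is equally exposed. Many subjects lost at a low score will already have a fall on record: under the assumptions in step 5, 88-98% of them had at least a 1-point fall recorded at baseline mean 9, and 66-89% at baseline mean 7.

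A reader might also infer that the 181 events become 263 or more. That needs unequal loss by risk factor. The 181 is moreover a worked example in a study with no fixed sample size or end date, illustrated there by phenoconversion, which occurs in unaffected carriers whom this mechanism hardly reaches. The completer slopes assume an analysis that the protocol does not plan, and the treatment of incomplete follow-up may be set out in an analysis plan that is not shown.

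Discretion does not cure the wording, however. The text covers every reason, gives no criteria and describes no follow-up afterwards. Data not collected under it are outside the reach of any analysis plan.

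**Conclusion.** The point holds as a wording defect with a real but unquantified risk. The clause allows outcome-related withdrawal of affected subjects, and that would usually understate progression. It needs to be reconciled with the provisions on incapacitated subjects, research proxies and retention.

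The size depends on how often sites use the clause, whether the last score is recorded, and the analysis. Under the assumed rates, completer slopes are about 5-25% too shallow, and models using all observed visits are off by about 0-15%, so modelling removes much of the bias but not reliably all of it. Equal loss of 10-30% of events would cut 80% power to about 76-65%. Hazard ratio attenuation is conditional on differential loss and should not be quoted as an expected effect. Severity: should fix.

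**What to change.** Reconcile section VII (Withdrawal from Participation) with sections IV, V and VI b:

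- Remove the words that extend the non-completion ground to every reason. State that inability to complete a procedure counts as a missed procedure and is not in itself a ground for study withdrawal.
- Keep such subjects in annual follow-up with whatever can be obtained: TFC with the companion or research proxy where consented, HD status and vital status.
- Record the reason each section was not done.
- Leave the subject-health ground and the best-interest ground as they are.

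The cost is a protocol wording change, one added CRF field and more partial visits in the database. Follow-up not collected now cannot reliably be recovered later.
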